##### Speed of implementation

The Stages of Implementation Completion [45] will be adapted to assess implementation progress of ATTAIN. This assessment tool includes eight stages that occur within three phases of implementation (pre-implementation, implementation, and sustainability). Scores are calculated for the speed of implementation as indicated by the amount of time spent in each stage, and the proportion of implementation activities completed.

##### Service outcomes

Mental health services access will be measured by documentation of successful completion of the first mental healthcare appointment and the proposed evidence-based practice that the mental healthcare provider will use. Communication between the referred-to mental health provider and referring primary care provider will be measured by documentation of a consultative interaction regarding the specified patient. These data will be extracted from the electronic health records of the children with whom providers reported using ATTAIN.

##### Covariates

Provider and caregiver sociodemographic variable will be available from the post-ATTAIN use online surveys. For child covariates, the following will be extracted from the electronic health records of children with whom providers used ATTAIN: sociodemographic characteristics, funding source for primary and mental healthcare, and documented mental health diagnoses, if any.

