#### Measures

The collaborative process will be assessed by the ATTAIN Advisory Group Collaborative Process Survey (AIM Study; PI: [name]; [43]) that will be administered at the conclusion of each group meeting.

### Aim 3

Aim 3 is to conduct an open trial feasibility pilot test of ATTAIN (directly informed by adaptations identified in Aim 2) in pediatric primary care offices. The primary implementation outcomes that will be measured are ATTAIN feasibility, acceptability, uptake, and speed of implementation. In addition, two primary service outcomes will be measured: mental health services access and communication between primary care and mental health provider.

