#### Procedure

Leadership at each primary care organization will be approached about their primary care practices participating in the pilot study. Primary care practices within each organization will be purposively selected for targeted recruitment of providers for ATTAIN implementation based on patient volume. Training in ATTAIN delivery will take place in advance of active implementation of ATTAIN. Subsequently, trained staff and providers will be asked to use ATTAIN with patients who have a documented ASD diagnosis during any outpatient appointment (e.g., annual check-ups, drop-in appointments) to maximize early detection of mental health problems and opportunity to link to mental health services. Quantitative data of ATTAIN use will be extracted from patient charts. After 4 months of ATTAIN delivery, participating providers and caregivers of youth with ASD with whom providers used ATTAIN will be asked to complete a brief online survey regarding their experiences using ATTAIN. Providers and staff will receive a $100 honorarium and caregivers will receive $20 for survey completion.

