##### Uptake

ATTAIN uptake will be measured using extracted data from the electronic health record system. Specifically, uptake will be defined as the proportion of ATTAIN-eligible patients (i.e., children with a documented ASD diagnosis) to the number children with whom providers used ATTAIN. Providers will be asked to self-report the patients with whom they used ATTAIN.

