#### Analysis

Descriptive statistics will first be conducted to characterize patterns of feasibility, acceptability, and uptake of ATTAIN over 4 months across and between the organizations that participated. Analyses of variance (ANOVA) will subsequently be performed to identify significant group differences in outcome measures between participating organizations. Additionally, the distribution of and correlations among provider, caregiver, and child covariates and outcome measures will be examined. Based on significant bivariate associations, subsequent linear regression models will be performed to identify predictors of the primary implementation outcomes. Given the pilot study design with explicit focus on feasibility, effect size estimation based on commonly used guidelines [46] will be emphasized.

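### Child and caregiver covariates exist only for children with whom ATTAIN was used, so the planned search for predictors of uptake cannot use them

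*Protocol article*

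**What the plan says.** All references are to the protocol article, Methods, Aim 3.

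- **Outcomes** (opening paragraph): "The primary implementation outcomes that will be measured are ATTAIN feasibility, acceptability, uptake, and speed of implementation".
- **Uptake**: "uptake will be defined as the proportion of ATTAIN-eligible patients (i.e., children with a documented ASD diagnosis) to the number children with whom providers used" (the model). Whichever way round that ratio is read, eligible children with whom ATTAIN was not used are part of it. Use is identified from providers: "Providers will be asked to self-report the patients with whom they used ATTAIN".
- **Child covariates** (Covariates): "For child covariates, the following will be extracted from the electronic health records of children with whom providers used ATTAIN". The items are sociodemographics, funding source for primary and mental healthcare, and documented mental health diagnoses.
- **Provider and caregiver covariates** (Covariates): "Provider and caregiver sociodemographic variable will be available from the post-ATTAIN use online surveys".
- **Who is surveyed** (Procedure, after 4 months of delivery): "participating providers and caregivers of youth with ASD with whom providers used ATTAIN will be asked to complete a brief online survey". No minimum level of use is set for providers.
- **Analysis**: "correlations among provider, caregiver, and child covariates and outcome measures will be examined". Then, where bivariate associations are significant, "subsequent linear regression models will be performed to identify predictors of the primary implementation outcomes". Neither sentence exempts uptake or restricts which covariates go with which outcome.

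**The concern.** The covariate sources and the planned analysis do not fit together for one of the four primary implementation outcomes. Uptake compares children with whom ATTAIN was used with all who were eligible. Child and caregiver characteristics are held for the first group only, so there is nothing to compare them with.

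The article states which records will be extracted and which analyses will draw on them, so this is not detail left to a fuller document. A later analysis plan cannot model covariates that were never extracted. If the text is followed, either the uptake models with child or caregiver covariates are dropped without notice, or they are fitted at provider level on averages that depend on the outcome. The second course is the riskier one, because the article says that effect sizes will be emphasised, and the effect size is what would be distorted.

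**Working it through.** The article gives no figure to reproduce here. The Aim 3 sample (60 providers approached, 45 expected, 45/60 = 75%) is set by precedent. The check is mainly one of structure.

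**Step 1: child level.** Let U = 1 if ATTAIN was used with an eligible child and 0 if not, and let X be a child covariate. X is recorded only when U = 1. Among children with X recorded, U is always 1, so Var(U) = 0. The correlation of X with U is undefined, and an odds ratio has two empty cells. This needs no assumption. As a check, children were simulated with an assumed true odds ratio of 2. With X on all eligible children the estimate was 2.01. With X only where U = 1, the variance of U was 0 and no odds ratio existed.

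**Step 2: caregiver level.** The survey goes only to caregivers of children with U = 1, so the same result follows.

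**Step 3: provider level.** Uptake can be summarised per provider as sum(U)/m, where m is the number of eligible children. The child covariate available for that provider is sum(X·U)/sum(U), in place of the case mix sum(X)/m. The available average is itself a function of U, the outcome, and cannot be computed when sum(U) = 0. So it describes the children the provider chose, not the children the provider saw. One assumed scenario (45 providers, 8 eligible children each, about 30% uptake, child-level odds ratio 2) gave a mean slope of uptake on the covariate of 0.140 with all eligible children and 0.019 with only those for whom ATTAIN was used. About 40 of the 45 providers could be kept. Part of that fall is noise, since each average rests on about 8 × 0.3 = 2.4 children. The figures illustrate the direction and do not estimate this study's bias.

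**Step 4: providers with no use.** These necessarily lack child and caregiver covariates. With a common uptake probability p and independent children, the expected number among 45 is 45 × (1 − p)^m. For example, m = 5 and p = 0.3 give 45 × 0.7^5 = 45 × 0.168 = 7.6. The article gives neither m nor p, so both are assumptions:

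| Eligible children per provider (m) | p = 0.1 | p = 0.3 | p = 0.5 |
|---|---|---|---|
| 3 | 32.8 | 15.4 | 5.6 |
| 5 | 26.6 | 7.6 | 1.4 |
| 10 | 15.7 | 1.3 | 0.0 |

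For the same mean uptake, variation in p between providers would raise these numbers.

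**Step 5: provider demographics.** All participating providers are asked to complete the survey, so these covariates are lost only through non-response. Uptake does not come from the survey, so a non-responder can have an uptake value and no demographics.

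**Step 6: where the covariates do fit.** Mental health services access and communication are extracted only for children with whom providers reported using ATTAIN (Service outcomes). For these outcomes the child covariates cover the analysis population.

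**The case against.** The strongest reply is that the article never states a child-level model of uptake. Uptake is a proportion, the regressions are linear, and the sentence on covariates and outcomes is generic. Child covariates may have been meant for the service outcomes, where they fit, and the pairing of covariates with outcomes could be left to a fuller plan. The study is also declared not to be powered for significance testing.

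Part of this stands. It limits the severity, and it means the service outcomes must be exempted. It does not remove the problem. The regressions are aimed at the primary implementation outcomes, which include uptake and not the service outcomes, and a provider-level model meets the difficulty in Step 3.

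Four stronger readings are tempting but not supported:

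- **Low-use providers drop out of the models.** The survey goes to all participating providers regardless of use, with a $100 honorarium. A provider with even one use contributes child data. Only zero-use providers necessarily drop out, and only from models with child or caregiver covariates.
- **Survey non-response biases the provider associations by a known amount.** This would require response to depend on use, which the article neither states nor excludes. No size can be given. Nothing says that uptake itself is computed on responders only.
- **The pilot fails its purpose because it cannot show which eligible children are missed.** The third objective is feasibility, acceptability and uptake. Profiling missed children is not a stated aim.
- **Diagnosis and mental health funding are circular predictors of service access.** They might be recorded after a child reaches care, but this is speculation. It would touch only the exploratory correlations, since the regressions target other outcomes.

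**Conclusion.** The concern holds for uptake. As written, child-level and caregiver-level predictors of uptake cannot be estimated, whatever the sample size, and this rests on the text alone. Provider-level summaries of child covariates can be computed but are conditioned on use. Zero-use providers have no child or caregiver covariates, and their number depends on eligible children per provider and on uptake, neither of which is given. Over the assumed grid it runs from 0.0 to 32.8 of 45. Provider demographics depend on a returned exit survey, which is avoidable but a lesser matter.

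Overall uptake, its comparison between organisations, provider-rated and caregiver-rated feasibility and acceptability, speed of implementation, and child-covariate analyses of the service outcomes are not affected by this point. It is a moderate issue in an exploratory pilot analysis.

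**What to change.** **Preferred.** Extract the same child covariates from the electronic health record for every ATTAIN-eligible child, whether or not ATTAIN was used. Take values recorded before ATTAIN use or, for the others, before the index visit, so that both groups are described at a comparable time. Collect provider demographics at enrolment or at the training that precedes implementation. State the level at which uptake is modelled; at provider level, average the covariates over all eligible children.

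This does not help caregiver covariates, because caregivers of the other eligible children are still not surveyed. Caregiver predictors of uptake should be excluded in either case.

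The cost is a wider query over patients who must already be identified for the uptake calculation, a few items moved from the exit survey to training, and possibly a privacy approval for the additional records from the university and each organisation's review board.

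**Alternative with almost no cost.** Restrict child-covariate and caregiver-covariate models to outcomes defined on children with whom ATTAIN was used, and state in the Analysis section that child and caregiver predictors of uptake will not be examined.

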#### Analysis

Descriptive statistics will first be conducted to characterize patterns of feasibility, acceptability, and uptake of ATTAIN over 4 months across and between the organizations that participated. Analyses of variance (ANOVA) will subsequently be performed to identify significant group differences in outcome measures between participating organizations. Additionally, the distribution of and correlations among provider, caregiver, and child covariates and outcome measures will be examined. Based on significant bivariate associations, subsequent linear regression models will be performed to identify predictors of the primary implementation outcomes. Given the pilot study design with explicit focus on feasibility, effect size estimation based on commonly used guidelines [46] will be emphasized.

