#### Participants

A total of 60 primary care providers will be recruited from primary care practices in the region. It is expected that 45 providers will agree to participate. This targeted sample size was chosen based on sample sizes used within completed pilot studies focused on service interventions in pediatric primary care [42]. Each provider will be asked to use ATTAIN with their pediatric patients who have a documented ASD diagnosis in the electronic health record over four consecutive months.

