### Limitations

Some methodological limitations warrant note. This study intentionally focuses on children with co-occurring ASD and non-ASD mental health conditions. It also comprises a developmental pilot study. The purpose of this design and approach is to systematically identify adaptations for implementation that can be tested in larger-scale trials and inform clinical implementation expansions to broader pediatric groups. As a result, this study is not statistically powered for traditional significance testing. However, effect size estimation [46] will be emphasized when interpreting quantitative study findings and is a more appropriate approach for pilot studies of feasibility.

Another limitation is the quasi-experimental study design. While this design is appropriate given the primary purpose of assessing the feasibility of ATTAIN implementation, the lack of randomization limits the extent of interpretation. One methodological decision to address this is capitalizing on variance vis-à-vis inclusion of three primary care organizations to assess implementation feasibility across diverse healthcare settings. Additionally, the inclusion of a community-academic partnership is a methodological advantage because community-academic partnership members can contextualize findings through their specialized organizational knowledge, which may bolster the clinical and implementation significance of results. Despite these limitations, this study has potential to further the field of integrated healthcare for children with ASD by accelerating identification of mental health problems in primary care and access to mental healthcare that may ultimately optimize child functioning and reduce expenditures.

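### Aim 3 regression predictors are screened by bivariate significance in a pilot that says it is not powered for significance tests, so small and moderate effects that survive are overstated

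*Protocol article*

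**What the plan says.** The Aim 3 Analysis section of the protocol article sets out a sequence. Descriptive statistics come first, within and across organizations. ANOVAs "will subsequently be performed to identify significant group differences in outcome measures between participating organizations". Correlations among provider, caregiver and child covariates and the outcomes are then examined. Last comes the regression step: "Based on significant bivariate associations, subsequent linear regression models will be performed to identify predictors of the primary implementation outcomes". The section closes by saying that effect size estimation will be given emphasis because this is a pilot.

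The Limitations section of the Discussion says that "this study is not statistically powered for traditional significance testing", and that "effect size estimation [46] will be emphasized when interpreting quantitative study findings and is a more appropriate approach for pilot studies of feasibility".

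On numbers, the Aim 3 Participants section says "A total of 60 primary care providers will be recruited from primary care practices in the region" and "It is expected that 45 providers will agree to participate". The size rests on precedent: "This targeted sample size was chosen based on sample sizes used within completed pilot studies focused on service interventions in pediatric primary care". The article states no alpha, no candidate count and no multiplicity rule for the screen.

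**The concern.** The article rejects significance testing as the basis for inference, then uses it as the rule that decides which covariates enter the regression models. The two positions conflict, and the conflict biases the estimates.

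In a small sample an association reaches significance only if its estimate happens to be large. Estimates that survive are therefore biased away from zero when the true effect is small or moderate, and real predictors of that size are often lost. Emphasising the size of a surviving estimate passes the selection bias on to the reader.

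The Impact section says the study's findings will inform a larger hybrid implementation effectiveness trial. If predictor results are carried into that trial, some would look stronger than they are, and other real ones would be missing.

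**Working it through.** **The plan's own figure.** The expected 45 providers are 75% of the 60 to be recruited (45/60 = 0.75). No effect size, standard deviation, alpha or power is given, so 45 cannot be derived from a formula. This agrees with the article's statement that the size follows earlier pilots.

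**Inputs.**
- n = 45 providers (Aim 3 Participants), with 60 as the upper case.
- Three organizations (Limitations: "capitalizing on variance vis-à-vis inclusion of three primary care organizations to assess implementation feasibility across diverse healthcare settings").
- Assumed: two-sided alpha 0.05, independent observations, and 15 providers per organization for the ANOVA.

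**Threshold of the screen.** A correlation is significant when |r| exceeds t/√(n − 2 + t²), where t is the 97.5% point of the t distribution on n − 2 degrees of freedom. At n = 45, t is about 2.017 on 43 df, so the threshold is 2.017/√(43 + 4.07) = 0.294. At n = 60 it is 0.254.

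**What passes, and how large it looks.** Simulation of 200,000 samples per row, n = 45:

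| True r | Passes the screen | Mean r if it passes | Ratio to truth | Mean r with no screen |
|---|---|---|---|---|
| 0.10 | 10% | 0.33 | 3.3 | 0.099 |
| 0.20 | 26% | 0.37 | 1.9 | 0.198 |
| 0.30 | 53% | 0.40 | 1.3 | 0.297 |
| 0.50 | 95% | 0.51 | 1.0 | 0.496 |

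A covariate with no true association that passes by chance shows a mean |r| of 0.35, which cannot be told apart from a true 0.20 or 0.30 that passed. A true 0.30 is discarded in 100% − 53% = 47% of studies. The last column shows that the screen causes the bias: without it the estimates are essentially unbiased.

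These are bivariate correlations. With one selected predictor the standardized regression slope equals r, so the inflation carries over in full. With several, the amount depends on how the predictors correlate.

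**If all 60 providers took part.** A true 0.20 passes 34% of the time and averages 0.33. A true 0.30 passes 65% of the time and averages 0.37. The problem is smaller but remains.

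**Organization comparison.** For three groups and n = 45 the critical F on 2 and 42 df is 3.22. With noncentrality n·f² = 45 × 0.25² = 2.81, power is about 28% at f = 0.25; at f = 0.40 it is 64%. With 60 providers, power at f = 0.25 is 37%. A significant result at n = 45 needs an observed eta-squared of at least 2(3.22)/[2(3.22) + 42] = 0.133, while f = 0.25 corresponds to a true value of 0.0625/1.0625 = 0.059. Overstatement follows only if significant contrasts alone are interpreted.

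**The case against.** This is an openly declared feasibility pilot. It discloses its lack of power, makes no confirmatory claim and says effect sizes will be emphasized. Its main results are descriptive. All of that stands and limits the weight of the point. It does not answer the regression step, because the article fixes a selection rule there and an effect size taken after that rule carries its bias.

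A reader might infer several stronger things that the article does not support:

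- **That the whole analysis is gated on significance.** It is not. The descriptive statistics, the ANOVAs and the correlations are all planned unconditionally; only the multivariable regression is filtered.
- **That the organization effect sizes are inflated too.** Nothing says they will be reported only for significant contrasts.
- **That effect sizes will be given without intervals, or in a metric that labels noise as an effect.** The article names no metric, and a condensed article that does not mention intervals has not excluded them.
- **That the predictors found will be mostly false.** This depends on how many candidates there are and how many are truly null, and neither is stated. For illustration, with k independent null predictor-outcome pairs the chance of at least one false selection is 1 − 0.95^k: 23% for k = 5 and 64% for k = 20, both values of k being assumed.
- **That n = 45 governs every model.** It is the provider count. The numbers of caregiver surveys and child records are not given, child records cluster within providers, and speed of implementation is not stated to be a provider-level measure.

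**Conclusion.** The point holds for the regression step. The stated selection rule contradicts the article's own basis for inference and biases the predictor estimates it yields. At 45 providers and an assumed alpha of 0.05, surviving estimates are about 1.9 times too large for a true correlation of 0.20 and 1.3 times for 0.30. There is practically no distortion at 0.50. A true 0.30 is lost nearly half the time.

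For the ANOVA the fault is the aim of finding significant differences with about 28% power at f = 0.25 (15 providers per organization assumed); bias there is conditional on how the results are read.

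This is a correction to exploratory analyses, worth making before they are run. It does not threaten the descriptive feasibility, acceptability and uptake results.

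**What to change.** In the Aim 3 Analysis section, or in the analysis plan that implements it:

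1. Remove the bivariate significance screen. Choose a short list of predictors for each outcome in advance, on the EPIS framework or other substantive grounds, and fit it whatever the p-values.
2. Replace the aim of finding significant group differences with estimation. Report organization differences and all examined associations as effect sizes with 95% confidence intervals, whatever their significance.
3. Label the organization comparisons and predictor models as exploratory.

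This changes wording only; data collection and sample size stay as they are. The small downside is that fewer covariates can enter the models, so some candidates will be reported only as unadjusted associations.

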**Fig. 1 Fig1:**
[figure not shown]
Application of the EPIS framework (adapted from [28]). Shaded components are the focus in this study

A key component within the EPIS framework and that is an essential implementation strategy within this study involves the inter-organizational relationships among stakeholders and entities. In this study, this is represented through community-academic partnership [30]. Specifically, community partnerships have been established with three primary care healthcare organizations in Southern California: (1) a linked health system with the largest pediatric primary care group in two Southern California counties, serving families with private insurance and Medicaid, (2) a private, for-profit integrated healthcare system that has a variety of payment systems including self-pay, employer-based private insurance, and subsidized programs, and (3) a federally qualified health center that serves a racially/ethnically/linguistically diverse and lower-income patient population along the US/Mexico border.

The “ATTAIN Advisory Group” will be developed to maximize the “fit” between ATTAIN and a range of pediatric primary care contexts. The ATTAIN Advisory Group includes stakeholders from the three healthcare organizations (described above) that serve children with ASD. The ATTAIN Advisory Group will be established at the outset of the study and meet regularly to guide study design choices, interpretation of results, implementation of findings in primary care settings, and evaluation of the collaborative process. The ATTAIN Advisory Group will include the principal investigator and approximately eight community stakeholders who represent pediatric and mental health providers, researchers, leaders, and caregivers of children with ASD.

Using key inner context factors from the EPIS framework, three objectives of this study will be pursued: (1) to identify targets to improve mental health screening and linkage to mental health services in primary care for children with ASD, (2) to adapt integrated care procedures to facilitate identification of mental health problems and linkage to evidence-based care for children with ASD, and (3) to examine feasibility, acceptability, and uptake of the adapted integrated mental healthcare model through a pilot study in pediatric primary care.

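### The Aim 3 predictor analysis states no adjustment for organization, so where site differences line up, a site effect can appear as a covariate effect or hide a real one

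*Protocol article*

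**What the plan says.** The protocol article, Methods, Aim 3, Analysis, sets out descriptive statistics and then an ANOVA of outcome measures between participating organizations. As a further step, "correlations among provider, caregiver, and child covariates and outcome measures will be examined", and then "Based on significant bivariate associations, subsequent linear regression models will be performed to identify predictors of the primary implementation outcomes". Effect sizes are to be emphasized.

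The Covariates subsection defines what is tested. For adults, "Provider and caregiver sociodemographic variable will be available from the post-ATTAIN use online surveys". For children, the record extract covers "sociodemographic characteristics, funding source for primary and mental healthcare, and documented mental health diagnoses, if any". Organization is in neither list. Its only stated inferential role is as the ANOVA grouping factor.

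The section on the conceptual framework describes the three organizations. The first is "serving families with private insurance and Medicaid". The second has "a variety of payment systems including self-pay, employer-based private insurance, and subsidized programs". The third is "a federally qualified health center that serves a racially/ethnically/linguistically diverse and lower-income patient population along the US/Mexico border". The Limitations section offers, as a response to the lack of randomization, "capitalizing on variance vis-à-vis inclusion of three primary care organizations to assess implementation feasibility across diverse healthcare settings".

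**The concern.** A correlation pooled over three sites combines two things: the association among people within a site, and the association between site averages. The organizations are described as differing in payer and, for the third, in income, race/ethnicity and language. Funding source and sociodemographics are among the covariates to be tested. If outcomes also differ by site, for instance through workflow or record system, part of that difference can be credited to a covariate. The ANOVA has the mirror problem: it is not adjusted for case mix, so neither analysis separates organization from who is served there.

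This is confounding of the coefficient. Allowing for clustering in the standard errors, or choosing covariates by another rule, would not remove it. Results are meant to guide implementation strategies and a larger hybrid trial, so a misattributed or missed predictor could misdirect that work.

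**Working it through.** **The plan's own figure.** The article expects 45 of 60 recruited providers (75%). It bases this on earlier pilots and gives no alpha, power or effect size, so there is no formula to reproduce. Split equally, 45/3 = 15 per organization (an assumption).

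**Algebra.** With equal site sizes,

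pooled covariance = within-site covariance + (1/3) Σ (site mean of x − overall mean of x)(site mean of y − overall mean of y).

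The second term carries the bias. Differences in both variables do not suffice; the patterns must be related. Outcome means (−1, 0, 1) with covariate means (1, −2, 1) give −1 + 0 + 1 = 0, so there is no bias.

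**Effect size.** Let f_y be Cohen's f for the outcome and f_x that for the covariate, with within-site SD of 1. If 40% of the covariate variance lies between sites, f_x = √(0.4/0.6) = 0.816. With no within-site association and fully aligned patterns, pooled r = f_y f_x / √[(1 + f_y²)(1 + f_x²)]:
- f_y = 0.25: 0.204/1.331 = 0.15
- f_y = 0.40: 0.327/1.390 = 0.23

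More data would not shrink these values.

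**False-predictor rate.** Simulation: 20,000 replicates per cell, 15 providers per site, no within-site association, two-sided 0.05. The three shares of covariate variance between sites are assumptions.

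| Pooled test | 20% | 40% | 60% |
|---|---|---|---|
| f_y = 0.25, random site patterns | 7.7% | 11.1% | 14.5% |
| f_y = 0.40, random site patterns | 12.3% | 19.3% | 27.9% |
| f_y = 0.25, aligned | 10.9% | 17.5% | 24.2% |
| f_y = 0.40, aligned | 20.1% | 34.5% | 50.2% |

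With organization as a fixed factor, the rate is 4.7-5.2% throughout. If sites do not differ in the outcome, the pooled test also keeps about 5%. A separate simulation of aligned patterns with f_x = 0.8 (share 0.64/1.64 = 39%) gave 17.3% and 34.9%, in agreement.

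**Masking.** Take a true within-site correlation of 0.45 with opposed site patterns and a 40% share. Pooled r becomes (0.45 − 0.204)/1.331 = 0.18 at f_y = 0.25 and (0.45 − 0.327)/1.390 = 0.09 at f_y = 0.40. Simulated power is 87% with organization in the model, against 20% and 6% pooled.

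**If a significant ANOVA brings organization into the regression.** Power of that ANOVA (3 groups, n = 45, df 2 and 42, noncentrality 45f²):
- f = 0.25: noncentrality 2.81, power 29%, so organization is left out in about 71% of studies
- f = 0.40: noncentrality 7.20, power 64%, so it is left out in about 36%

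Under this rule, with aligned patterns, f_y of 0.25 to 0.60 and f_x of 0.4 to 1.2, the false-predictor rate is about 3-9%. Masking is not relieved: the covariate must first pass the pooled screen, so power cannot exceed 20% and 6% in the case above.

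**The case against.** The strongest reply is that the article never says the correlations are pooled or that organization is left out. That is so; both are inferred from the covariate lists and from the lack of any stated stratification or adjustment. The Covariates subsection lists what must be collected, and organization is known without collection. An ANOVA of outcome by organization could itself count as a bivariate association. That reading is fair and brings false predictors close to the nominal level, but it rests on an underpowered entry test and leaves masked predictors unprotected.

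The article also calls the study unpowered for significance testing, emphasizes effect sizes and accepts limited interpretation without randomization. This limits the harm to exploratory results. It does not remove the problem, because the pooled effect size carries the same mixture and entry to the regression still depends on significance. A marginal association can be a legitimate descriptive target, but it should then be labelled as one that includes site differences.

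Three stronger inferences are not supported:
- A reader might infer that any site difference in both covariate and outcome biases the result. The counterexample above shows that the patterns must be aligned or opposed.
- A reader might infer that a child's funding source could be reported as a predictor of uptake. Child covariates are extracted only for children with whom ATTAIN was used, so that child-level model cannot be fitted.
- A reader might take the 40% share as a property of these sites. The article gives no payer shares, describes income, ethnicity and language for the third organization only, and says nothing on how provider characteristics vary between sites.

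**Conclusion.** The point holds as a weakness in the stated method: the covariate screen and predictor regressions carry no stated adjustment for organization, in a study whose sites differ in payer and patient mix. When site patterns are aligned or opposed, the direction of the distortion follows from the algebra. Its size does not come from the documents. At the assumed 40% share, 15 providers per site and outcome f of 0.25 to 0.40, the false-predictor rate is about 11-19% over random patterns and 17-35% if aligned, against 5% with adjustment. On the favourable ANOVA reading it is about 3-9%. Without an outcome difference between sites there is no inflation. The analyses affected are exploratory parts of a pilot, so this calls for a correction of the analysis wording and does not undermine the feasibility aims.

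**What to change.** Revise the Aim 3 Analysis section along these lines: associations of provider, caregiver and child covariates with the implementation outcomes will be estimated with organization as a fixed factor, and every predictor regression will include organization whatever the ANOVA result. Organization differences will be shown both unadjusted and adjusted for case mix. Where a covariate varies too little within organizations to be separated from them, this will be stated and the covariate will not be reported as a predictor. All predictor results will be labelled exploratory.

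The change is to wording only, since organization is already known for every participant. With three organizations it uses two degrees of freedom (for one covariate and 45 providers, residual df falls from 43 to 41). Intervals widen for covariates closely tied to organization, which reflects how little the data can say about them apart from site.
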